## Abstract

**Background:**

Older adults can benefit from physical activity in numerous ways. Physical activity is considered to be one of the few ways to influence the level of frailty. Standardized exercise programs do not necessarily lead to more physical activity in daily life, however, and a more personalized approach seems appropriate. The main objective of this study is to investigate whether a focused, problem-oriented coaching intervention (‘Coach2Move’) delivered by a physiotherapist specializing in geriatrics is more effective for improving physical activity, mobility and health status in community-dwelling older adults than usual physiotherapy care. In addition, cost-effectiveness will be determined.

**Methods/Design:**

The design of this study is a single-blind randomized controlled trial in thirteen physiotherapy practices. Randomization will take place at the individual patient level. The study population consists of older adults, ≥70 years of age, with decreased physical functioning and mobility and/or a physically inactive lifestyle. The intervention group will receive geriatric physiotherapy according to the Coach2Move strategy. The control group will receive the usual physiotherapy care. Measurements will be performed by research assistants not aware of group assignment. The results will be evaluated on the amount of physical activity (LASA Physical Activity Questionnaire), mobility (modified ‘get up and go’ test, walking speed and six-minute walking test), quality of life (SF-36), degree of frailty (Evaluative Frailty Index for Physical Activity), fatigue (NRS-fatigue), perceived effect (Global Perceived Effect and Patient Specific Complaints questionnaire) and health care costs.

**Discussion:**

Most studies on the effect of exercise or physical activity consist of standardized programs. In this study, a personalized approach is evaluated within a group of frail older adults, many of whom suffer from multiple and complex diseases and problems. A complicating factor in evaluating a new approach is that it may not be automatically adopted by clinicians. Specific actions are undertaken to optimize implementation of the Coach2Move strategy during the trial. Whether or not these will be sufficient is a matter we will consider subsequently, using quality indicators and process analysis.

**Trial Registration:**

The Netherlands National Trial Register: NTR3527.

## Background

Physical activity is considered one of the few ways to influence frailty in older adults [1-4]. The extent to which the level of frailty can be influenced by physical activity remains unclear, however. Frailty is defined as a complex state of increased vulnerability to adverse health outcomes [5]. The causes as well as the consequences of frailty are diverse and originate from multiple dimensions (physical, psychological and social), which makes frailty a difficult concept to measure [6]. A small number of studies have shown a positive effect of physical activity on the level of frailty by measuring physical aspects of frailty [7,8]. The positive effect of exercise on other frailty-related aspects of health, for example, mood and cognition, has also been confirmed in studies [9,10]. The complex interaction between the physical, psychological and social dimensions of frailty influences the level of frailty. The total level of frailty is, therefore, not equivalent to the sum of its components. When, for example, muscle strength improves because of an exercise intervention, this could lead to better mobility and the ability to become more physically active. Also, it may become easier to go outdoors, which can positively influence mood and social interaction. As a consequence, when all these dimensions are taken into account, the level of frailty may improve by even more than the levels of the separate components. The multidimensional level of frailty, considering all aspects of frailty in interaction using one measurement instrument, has not been evaluated in intervention studies on exercise and physical activity hitherto.

Furthermore, while the positive effect of physical activity on different aspects of health is widely accepted, many older adults remain sedentary [11]. Standardized supervised exercise interventions do not necessarily increase the level of physical activity in daily life [12]. It is a great challenge to attain the behavioral change that is necessary to become more physically active in the long term and to improve adherence to physical activity programs or interventions. Individually adapted programs that aim for participants to become more physically active in daily life are probably more (cost-) effective [13]. We have developed an individual intervention aimed at promoting physical activity in the broad population of older adults suffering from or at risk of mobility problems. Most older adults have to deal with multiple and complex problems and diseases, and yet often they do not fulfil the specific inclusion criteria used in clinical studies. Therefore, we developed an intervention aimed at a very broad population of older adults. Because of the complexity of this intervention, the Medical Research Council (MRC) framework was used as a guide in developing the intervention. The MRC framework consists of five successive phases: preclinical or theoretical phase (phase I), modelling phase (phase II), exploratory trial (phase III), randomized controlled trial (phase IV), and long-term implementation (phase V). In the theoretical phase, we performed two systematic reviews. The first review deals with instruments for measurement of frailty. In this review, we concluded that numerous measurement instruments exist, but none of them has been developed as an outcome measure [6]. Therefore, we subsequently developed an outcome instrument on frailty; the Evaluative Frailty Index for Physical Activity (EFIP) [14]. In a second article, we review the literature on the effect of physical exercise therapy in older adults who have problems with physical functioning and/or have to deal with co-morbidity [12]. The included literature was evaluated in meta-analyses and we concluded that mobility and physical functioning are positively influenced by physical exercise therapy. Strength training also seemed to be of great importance and a personalized approach may result in long-term positive effects (>12 months). No positive effects on quality of life and the level of physical activity could be found, which confirms that an exercise intervention does not necessarily bring about changes in level of physical activity.

In the modelling phase of the MRC framework, we developed the intervention based on the findings from the theoretical phase and expert consultation. This process will be described in detail in another publication. The intervention was called ‘Coach2Move’ and is based on clinical reasoning conforming with the Hypothesis Oriented Algorithm for Clinicians (HOAC)-II [15,16] and the International Classification of Functioning, Disability and Health (ICF) [17]. The HOAC-II is an algorithm for clinical reasoning that describes all steps to be taken in order to make appropriate decisions about the treatment of patients. The steps of the HOAC-II were specified for the physiotherapy treatment of frail older adults with mobility problems in the Coach2Move strategy. The core elements of the Coach2Move strategy are: 1) increasing the level of physical activity and (social) participation; 2) patient-identified goals, and thereby improving adherence; 3) enablement instead of disablement (what a patient can do instead of what a patient cannot do); and 4) self-management. The Coach2Move strategy was tested for feasibility and efficacy in a pilot study ([name] *et al*., unpublished observations). The results of this pilot study showed that the Coach2Move strategy is well appreciated by both physiotherapists and patients and that a positive effect on physical activity, mobility, frailty and quality of life can be expected. The present article describes the study design of a Randomized Controlled Trial (RCT) to evaluate the Coach2Move strategy. The main objective of this RCT is to test the hypothesis that the Coach2Move strategy delivered by a physiotherapist specializing in geriatrics is more effective in improving physical activity in community-dwelling older adults than is usual physiotherapy care. As a secondary objective, the effect of the Coach2Move strategy on the (multidimensional) level of frailty, mobility and quality of life, as well as cost-effectiveness, will be assessed in comparison with usual physiotherapy.

## Methods/Design

### Study design

The study design is a single-blinded randomized controlled trial (RCT) in which the consort guidelines are being followed. The RCT is being performed in thirteen physiotherapy practices. In each participating practice both a general physiotherapist (PT) and a PT specializing in geriatrics (GPT) will participate in the study. Participating GPTs will be trained in the Coach2Move strategy. The PTs will provide the usual care.

### Participants

The population consists of (pre-)frail older adults with mobility problems and/or a physically inactive lifestyle who are at risk of loss of mobility in the near future. This study focuses on elderly people living relatively independently at home or in a home for elderly people. Older adults with acute health problems for which hospital admission or admission to a nursing home is necessary are excluded. Older adults signed up for physiotherapy are considered for inclusion, whether referred by a physician or having decided to attend physiotherapy by themselves.

The inclusion criteria are as follows:

1. Older adults aged ≥ 70 years living independently at home or in an older persons’ home.

2. A mobility problem and/or a physically inactive lifestyle (< 30 minutes per day) rated as such by the participant, their relatives or the referring physician.

The exclusion criteria are as follows:

1. Unable to walk 5 meters (waling aid allowed).

2. Unable to follow verbal or written instructions, operationalized by a minimum score of 21 points on the Minimal Mental State Examination (MMSE), or unable to understand Dutch.

3. Palliative phase of illness.

4. Acute illness with hospital indication.

5. Severe degenerative neurological illness.

6. Having a contraindication for being physically active.

7. Having had physiotherapy for a period longer than four weeks during the last six months.

### Randomization, blinding and treatment allocation

All older adults (≥70 years old) who sign up for physiotherapy in one of the participating physiotherapy practices, because of mobility problems and/or physical inactivity are asked to participate in the trial by either a physiotherapist or a practice secretary. If willing to participate, they are called by a member of the research team within two days. The member of the research team will determine potential eligibility by telephone and make an appointment for baseline measurement. An informed consent form is signed by both the participant and the research assistant before the baseline measurement. The final decision on inclusion or exclusion and randomization takes place after baseline measurement. Randomization is done on the individual level through a computer-generated random-sequence table. Pre-stratification is applied by physiotherapy practice. Opaque, sequentially numbered, sealed envelopes are prepared for each stratum (that is, physiotherapy practice) by a researcher who is not involved in enrolling the participants, in assigning them to their groups or performing follow-up measurements. Each of the envelopes contains a sheet of paper indicating one of the two interventions. The sealed envelopes are delivered to the participating physiotherapists or practice secretaries after baseline measurement. Participants learn their group assignments after the researcher or research assistant involved in the baseline measurement has left. Follow-up measurement at three and six months is performed by two research assistants who are unaware of group allocation.

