#### *Uncorrected sample size*

In our pilot study of ten patients treated by one of two therapists, we found on log scale an increase of 1.21 from baseline and a standard deviation of 1.0 (in the pre-intervention scores). This corresponds to a 3.35 fold increase from baseline scores on the untransformed LAPAQ scale. The control group in our study is comparable to the experimental group in the study performed by Rubenstein *et al*., which found a 20% increase from baseline (1.2-fold increase) [32]. Thus the intervention is estimated to be 3.35/1.2 = 2.8 times as effective as the control treatment. To account for possible overestimation of the effect by the pilot study and possible contamination, we assume that at least 60% of this effect will be retained; that is, the intervention is at least 1.68 times as effective as the control. Then, the effect on log scale is 0.5 (sd = 1.0 as above). The uncorrected sample size to detect this difference with 80% at a significance level of 0.05 is 64 patients per group.

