#### *Clustering*

In our pilot study we found ICC = 0 and, conservatively setting the ICC = 0.05, the correction for clustering is 1 + (n-1)*0.05. Allowing for maximal 20% dropout, the corrected sample size can be calculated with: 64*0.64*(1 + (n-1)*0.05)* 1/(80%). Table 2 gives the sample sizes when a different number of physiotherapy practices are included. If each participating physiotherapist (2 per practice, 13 practices = 26 physiotherapists, 12 physiotherapists per group) were to treat 5 patients, a total number of 130 patients would be included (65 patients per group). This is more than the 62 patients per group necessary according to the power calculation (see Table 1). If each therapist were to treat four patients, however, the power would not be reached. Therefore we will include 65 patients per group (total = 130) in this trial.

**Table 2 T2:** Sample size calculation

**n = Number of patients per cluster**	**Sample size per group: 64*0.64*(1 + (n-1)*0.05)* 1/(80%)**	**#Clusters group: sample size /n**
10	75	8
9	72	8
8	70	9
7	67	10
6	64	11
5	62	13
4	59	15

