### Statistical analysis

Descriptive statistics will be used to present group characteristics on age, education, marital status, multi-morbidity, level of frailty, number of post-operative patients, therapy adherence and adverse effects. Any asymmetry between the intervention and control group on these variables at baseline will be statistically corrected. The effects of the intervention are analyzed according to the intention-to-treat principle. The analysis of the primary and secondary outcome measures employed a linear mixed model to relate the three- and six-month outcomes to the effect of the treatment. Therapist is taken as a random effect in this model to account for the clustering of patients with therapists. Measurement (baseline, 3 months, 6 months) is included as a random effect to account for correlation of measurements over time. Because this analysis uses all three measurements (baseline, 3 and 6 months), it will actually be more powerful than an ANCOVA analysis and the power of the study will be more than 80%.

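### The stated mixed model leaves out practice, the stratification factor, so standard errors are somewhat too wide if practices differ

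*Protocol article*

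**What the plan says.** **Design.** The Study design section pairs the therapists: "In each participating practice both a general physiotherapist (PT) and a PT specializing in geriatrics (GPT) will participate in the study". The geriatric physiotherapist delivers Coach2Move and the general physiotherapist delivers usual care. Under Randomization, blinding and treatment allocation, "Randomization is done on the individual level through a computer-generated random-sequence table", and "Pre-stratification is applied by physiotherapy practice". Each practice is therefore a stratum containing one therapist from each arm.

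**Analysis.** The Statistical analysis section describes a linear mixed model for the primary and secondary outcomes. On clustering it says "Therapist is taken as a random effect in this model to account for the clustering of patients with therapists". The only other random effect named is time: "Measurement (baseline, 3 months, 6 months) is included as a random effect to account for correlation of measurements over time". Adjustment is foreseen for a list of patient characteristics: "Any asymmetry between the intervention and control group on these variables at baseline will be statistically corrected". Practice is neither on that list nor in the model.

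**Sample size.** The planning ICC is defined as the correlation of patients within a therapist. It was 0 in the pilot and is set to 0.05. No between-practice variance is given.

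**The concern.** The two therapists of a practice are likely to share a catchment area, case mix and referral pattern. Randomising within practice removes those shared features from the treatment comparison, because they raise or lower both arms alike.

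A model with 26 unpaired therapist effects does not know this. It estimates one between-therapist variance, which includes the shared practice component, and charges all of it to the treatment contrast. At stake are confidence intervals wider than the design warrants and a test with a true size below 5%, for the primary outcome and every secondary outcome analysed this way.

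**Working it through.** **Inputs from the article**
- 13 practices and 26 therapists, hence 13 per arm. The Clustering section reads "2 per practice, 13 practices = 26 physiotherapists, 12 physiotherapists per group"; I use 13, because 26 / 2 = 13.
- 65 patients per arm, 5 per therapist. With 20% dropout, 65 × 0.80 / 13 = 4 completers per therapist (m = 4).
- Effect and SD: "Then, the effect on log scale is 0.5 (sd = 1.0 as above". The baseline-adjustment factor is 0.64 and the within-therapist ICC is 0.05.

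**Assumptions**
- Test two-sided at 0.05, balanced clusters, and one baseline-adjusted outcome with variance 0.64 to which the ICC applies.
- A share s of the ICC lies at practice level. It is not in the article, so I let it run from 0 to 100%. Each therapist works in one practice, so the within-therapist ICC already contains any practice component.

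**The plan's own figures.** A two-sided t-test with 64 per group has power 0.801 for an effect of 0.5 SD. With 5 patients per therapist, 64 × 0.64 × (1 + 4 × 0.05) / 0.80 = 61.44, rounded up to 62. Both figures reproduce.

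**Standard error of the treatment effect**
- What the therapist-only model reports: √(2 × 0.64 × [ICC + (1 − ICC)/m] / 13)
- True value, with practice cancelled: √(2 × 0.64 × [ICC − s × ICC + (1 − ICC)/m] / 13)

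For ICC 0.05 and m = 4 the bracket in the first formula is 0.05 + 0.2375 = 0.2875, giving √(2 × 0.184 / 13) = 0.168. In the second formula the bracket is 0.2875, 0.2625 or 0.2375 for s = 0, 50 or 100%. The factor 0.64 cancels in the ratio.

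| Practice share of ICC 0.05 | Reported SE | True SE | Ratio |
|---|---|---|---|
| 0% | 0.168 | 0.168 | 1.00 |
| 50% | 0.168 | 0.161 | 1.05 |
| 100% | 0.168 | 0.153 | 1.10 |

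With no dropout (m = 5) the ratios are 1.00, 1.06 and 1.12.

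**Type I error and power.** In this balanced setting, leaving practice out amounts to an unpaired t-test on therapist means (24 df). Practice as a fixed effect amounts to a paired t-test (12 df). Simulation at m = 4 and ICC 0.05 gives:

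| Practice share | Type I error, practice omitted | Power, omitted | Power, fixed practice | Power, random practice |
|---|---|---|---|---|
| 0% | 5.0% | 81% | 78% | 83% |
| 50% | 4.0 to 4.1% | 82 to 83% | 81 to 82% | 85% |
| 100% | 3.2 to 3.4% | 83 to 84% | 85% | 87% |

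Ranges are the spread between simulation runs of 40,000 and 400,000 trials. Fixed practice effects held 5% throughout. The random intercept used 12 df when the estimated practice variance was positive and 24 df when it was truncated at zero. Its type I error was then about 5.5 to 6.3%, so part of its power gain comes from that excess. With 12 df throughout, its type I error was 5.2 to 5.7%.

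**Beyond the planning value.** With ICC 0.10, all at practice level, and m = 4, the two SEs are √(2 × 0.208 / 13) = 0.179 and √(2 × 0.144 / 13) = 0.149, a ratio of 1.20. Type I error is then about 2.1%, and power is about 80% with practice omitted against 87% with fixed practice effects.

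**The case against.** **The article is condensed.** It does not say that the named effects are the whole model, and stratum terms are often fixed in an analysis plan, which is not shown. It remains possible that practice is included there. But the article does set out the clustering structure, and that structure does not match the design it describes. The point is about a stated specification.

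**The loss may be nil.** The pilot ICC was 0, and baseline physical activity in the model would absorb part of any case-mix difference between practices. Both are fair. The pilot had only ten patients and two therapists, so its ICC says little. The honest range still starts at zero.

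**Adding practice is not free.** As a fixed effect it halves the therapist-level degrees of freedom. At the planning ICC, power then changes by only about −3.5 to +1.6 points. This stands, and it bears on which form of the term to choose.

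**Stronger readings that the article does not support**
- A reader might infer that the stratification is wasted. It is not: it still balances the arms within practices and lowers the true variance of the estimate. Only the reported standard error fails to show this.
- A reader might infer that the trial is underpowered. The sample size carries the full therapist-level design effect with no credit for pairing, which agrees with a therapist-only model.
- A reader might add practice variance on top of a 5% therapist variance and reach inflations of 13% or 26%. That needs a within-therapist ICC of 0.10 or 0.15, two to three times the planning value.

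**Conclusion.** The mismatch is real and its direction is clear: if practices differ, the stated model overstates the standard error and the test is conservative. It does not bias the effect estimate or raise the false-positive rate. At the planning ICC of 0.05 with 4 completers per therapist, the overstatement lies between 0% and about 10%, with a true type I error between 5.0% and about 3.3%. Larger effects arise only if the within-therapist ICC exceeds 0.05. These sizes rest on an assumed practice share, balanced clusters and a single baseline-adjusted outcome; the direction does not depend on them. The stated sample size and 80% power stand. This is a worthwhile correction to precision and to the nominal size of the test, not a fatal flaw.

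**What to change.** Pre-specify practice (13 strata) in the models for the primary and secondary outcomes, preferably as a random intercept with therapist nested within practice, and state the degrees-of-freedom method. The choice should be made before any unblinded data are seen.

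The cost is one model term and a choice between two modest drawbacks:
- **Random intercept (preferred).** It largely avoids the loss of degrees of freedom. With only 13 practices it can give slightly more than 5% type I error when the practice variance is estimated as zero. A small-sample degrees-of-freedom correction keeps this excess small; in the check above, a conservative 12 df left 5.2 to 5.7%.
- **Fixed effects.** These hold 5% but cut the therapist-level degrees of freedom from 24 to 12 and can cost about 3 to 4 points of power if practices do not differ.

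If the full analysis plan already contains practice, it is enough to say so and to name the form. No change to the sample size is needed.
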